### Aims and Objectives

The primary objective of this study is to evaluate the safety and tolerability of short- and longer-term administration of dovramilast in adults with new or recurrent ENL. Secondary objectives include assessing preliminary clinical signals of efficacy, including changes in ENL severity, pain, and neurological symptoms, as well as documenting patterns of remission and recurrence. Exploratory objectives include evaluating biological correlations of treatment response using plasma and skin biopsy samples to support mechanistic understanding.

### Study Setting and Sites

The study will be conducted at Anandaban Hospital, The Leprosy Mission Nepal, located in Lalitpur District, Nepal, along with its affiliated satellite clinics. Anandaban Hospital is a national referral center for leprosy and leprosy-related complications and provides specialized clinical and research infrastructure for ENL management and follow-up.

### Sample Size and Justification

The planned sample size includes 10 male participants in step 1 and up to 40 additional male and female participants in step 2. Anandaban Hospital is a tertiary referral center for the management of leprosy reactions and related complications, with approximately 60 to 70 patients with ENL presenting annually. A target sample size of 40 participants was selected based on feasibility considerations, recognizing that not all presenting patients would meet the study’s inclusion criteria or be eligible for enrollment.

Moreover, as this is an observational pilot study, no formal statistical power calculation was performed. The selected sample size is intended to allow assessment of feasibility, safety, and variability in clinical outcomes and to generate preliminary evidence to inform the design and sample size estimation of a future multicenter randomized controlled trial.

### ENL Case Definition

ENL definitions are aligned with the ENL International Study Group definitions [19] and the EESS [24]. ENL is defined as occurring when an individual diagnosed with BL or LL leprosy and a bacterial index >3+ develops 10 or more tender papular or nodular or both types of skin lesions. Other ENL symptoms may also be included but not be limited to those listed in the EESS.

There are 3 clinical patterns by which ENL is described [24]:

Acute for a single episode lasting less than 24 weeksRecurrent if a patient experienced a second or subsequent episode of ENL occurring 28 days or more after stopping treatment for ENLChronic if occurring for 24 weeks or more during which a patient has required ENL treatment either continuously or where any treatment-free period had been 27 days or less

This initial phase 2 clinical trial will focus on acute and recurrent forms of ENL.

The EESS [24] will be used to establish the presence and severity of ENL symptoms during the trial.

### Study Design

#### Overview

This study will be a single-center, single-arm, phase 2, open-label trial to evaluate the safety and efficacy of 200 mg dovramilast administered twice daily and consumed with fatty food in participants with moderate-to-severe ENL. As outlined in Figure 3, the study will be performed in 2 steps.

**Figure 3. F3:**
[figure not shown]
Overall study design showing treatment decision process and treatment durations. CRP: C-reactive protein; ENL: erythema nodosum leprosum; ENLIST: Erythema Nodosum Leprosum International Study Group; HepB: hepatitis B; HepC: hepatitis C; RA: rheumatoid arthritis; TB: tuberculosis; VDRL: Venereal Disease Research Laboratory test for syphilis. Created in BioRender [26].

Step 1: 10 male participants with new or new episode ENL.Step 2: Up to 40 participants, including male and female patients with new or new episode ENL.

The primary aims of step 1 and step 2, respectively, are as follows:

To evaluate the immediate effect on the safety and efficacy of 28 days (1 mo) of dovramilast treatment in 10 males with a new or recurrent episode of ENLTo evaluate a 12-week treatment cycle of dovramilast, with the provision for further 12-week treatment cycles of dovramilast for up to 48 weeks (12 mo), in up to 40 participants, including males and females presenting with new or recurrent ENL

A safety analysis will be conducted on all participants who received at least 1 dose of the study drug and will include the frequency of all AEs and laboratory abnormalities (Figure 4), as well as the frequency of dose interruptions, dose reductions, and treatment discontinuations.

**Figure 4. F4:**
[figure not shown]
List of laboratory tests to be performed during the trial. The asterisk (*) indicates the subset of tests performed in step 1. All tests will be performed in step 2. Created in BioRender [26].

Study participants will be eligible for any concomitant treatment, including, but not limited to, WHO-recommended MDT, antipyretics, and analgesics. No standard ENL treatment regimens of prednisolone or thalidomide, or both, will be provided during the study drug treatment. In step 1, any new ENL episodes after the cessation of the study drug will be managed with standard ENL care. In step 2, any new ENL episodes will be managed with a repeat 12-week treatment cycle with dovramilast.

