### Treatment for ENL

Prednisolone, thalidomide, and clofazimine are currently recommended by the WHO as treatment for ENL; however, ENL treatment has been controversial for decades [20,21,28,35,36]. Prednisolone is the most common first-line treatment in most low- or middle-income countries and leprosy-endemic countries (except Brazil, which uses thalidomide). Prednisolone is generally available and affordable, but, as ENL may require years of treatment, patients can develop severe consequences such as diabetes, cardiovascular problems, blindness, and osteoporosis leading to bone fractures [37-39].

Thalidomide, the most recently recommended therapeutic agent for the treatment of ENL, was developed more than 50 years ago and has both immunoregulatory and sedative activity [40]. However, owing to the teratogenicity and related consequences in the 1960s, thalidomide is often restricted or unaffordable for most ENL cases in endemic countries. High-dose clofazimine has anti-inflammatory properties and can be given in combination with prednisolone. Studies, however, have not indicated a significant impact, and patients rarely tolerate clofazimine due to skin pigmentation [41].

Both high-dose prednisolone and thalidomide are sometimes insufficient to control severe refractory ENL [42-44]. Many cases are chronic and experience ENL symptom relapse soon after the decrease in dosage or cessation of drugs [35]. Thus, a safe and effective drug that can be used for a shorter duration and imparts long-term remission has always been envisioned [28]. These problems are compounded by the lack of alternative treatments with established efficacy for ENL. Various efforts have been made to develop alternative ENL treatments, most notably pentoxifylline, azathioprine, cyclosporine, methotrexate, and anti-TNF biologics such as etanercept and infliximab [45-59].

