**Figure 2. F2:**
[figure not shown]
Chemical structures of dovramilast and thalidomide. Figures were drawn using the RCSB PDB Chemical Sketch Tool with chemical Simplified Molecular-Input Line-Entry System (SMILES) from PubChem.

Therefore, the primary objective of this phase 2, open-label clinical trial is to evaluate the safety and preliminary efficacy of dovramilast in adults with new or recurrent ENL. The primary research question is whether dovramilast is safe and well tolerated when administered for short- and longer-term treatment cycles in patients with ENL. Secondary research questions address whether dovramilast treatment is associated with improvements in ENL severity, pain, and clinical manifestations over time, and whether repeated treatment cycles can reduce recurrence without the need for prolonged corticosteroid or thalidomide use. We hypothesize that dovramilast will demonstrate a favorable safety profile and lead to clinically meaningful reductions in ENL severity and symptom burden, supporting its further evaluation as an alternative therapeutic option for ENL.

This protocol is written based on SPIRIT (Standard Protocol Items: Recommendations for Interventional Trials) guidelines (Checklist 1) [70].

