### Exclusion Criteria

The presence of any of the following will exclude a potential participant from enrollment:

Any significant medical condition, laboratory abnormality, or psychiatric illness that would prevent the participant from participating in the study.Daily rifampicin treatment will be excluded with a minimum washout period of 2 weeks prior to dovramilast administration. However, if rifampicin is taken only once a month as part of MDT, this will not be used as an exclusion criterion.Any condition, including the presence of laboratory abnormalities, that places the participant at an unacceptable risk if they were to participate in the study.Any condition that confounds the ability to interpret data from the study (ie, HIV, chronic hepatitis B, chronic hepatitis C, or tuberculosis in patients under active treatment). Patients with resolved tuberculosis will not be excluded from the study.Use of systemic corticosteroids or thalidomide within 7 days of study medication initiation.Pregnant or nursing females.

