### Primary and Secondary Outcomes

The primary outcome is the proportion of participants achieving a complete clinical response by day 10 of dovramilast treatment. Complete clinical response is defined as a clinically meaningful improvement or resolution of ENL manifestations based on standardized clinical criteria rather than a binary presence or absence. This includes a reduction in the number, tenderness, and inflammation of ENL skin nodules, assessed clinically and supported by changes in the EESS score; resolution of ENL-associated fever based on clinical assessment and temperature recordings; and improvement or resolution of nerve pain and tenderness evaluated through neurological examination and validated pain assessment tools. Safety outcomes include the frequency and severity of AEs, graded according to the National Cancer Institute Common Terminology Criteria for Adverse Events (NCI CTCAE) version 5.0 [71], as well as laboratory abnormalities and neurological assessments. In addition, plasma and skin biopsy samples will be collected at predefined time points for exploratory evaluation of biological responses to dovramilast, including inflammatory and immunological markers relevant to ENL pathogenesis (such as circulating cytokines, acute-phase reactants, and immune cell–associated markers), and histopathological features of ENL lesions. These exploratory analyses will be descriptive and are intended to provide mechanistic insights into treatment response.

Secondary outcomes include the proportion of participants who achieve and maintain remission of ENL symptoms during treatment and for up to 12 months following cessation of the study drug. Longitudinal changes in disease severity, pain, and neurological symptoms will be assessed over time using validated instruments, including the EESS, Brief Pain Inventory, and Douleur Neuropathique 4 questionnaire. In addition, the frequency of ENL recurrence and the need for repeat dovramilast treatment cycles during the follow-up period will be documented.

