## Discussion

### Principal Findings

This phase 2 study is designed to evaluate the safety, tolerability, and preliminary clinical effects of dovramilast in patients with new or recurrent ENL. We hypothesize that dovramilast will demonstrate an acceptable safety profile and be associated with clinically meaningful reductions in ENL severity and symptom burden, while reducing reliance on prolonged corticosteroid or thalidomide therapy. If confirmed, these findings would support further evaluation of dovramilast as a novel immunomodulatory treatment option for ENL.

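### Two of the three parts of the day-10 response can be improved by freely permitted antipyretics and analgesics, and the corticosteroid/thalidomide-sparing question has no outcome behind it

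*Protocol article*

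**What the plan says.** Methods, Study Design, Overview (the paragraph after the Figure 4 legend) sets the co-medication rule: "Study participants will be eligible for any concomitant treatment, including, but not limited to, WHO-recommended MDT, antipyretics, and analgesics". The next sentence limits it: "No standard ENL treatment regimens of prednisolone or thalidomide, or both, will be provided during the study drug treatment". The same paragraph sends new episodes after study drug to standard ENL care in step 1 and to a further dovramilast cycle in step 2. The Exclusion Criteria add two restrictions on prior treatment: "Use of systemic corticosteroids or thalidomide within 7 days of study medication initiation", and "Daily rifampicin treatment will be excluded with a minimum washout period of 2 weeks prior to dovramilast administration".

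Methods, Primary and Secondary Outcomes builds the day-10 complete clinical response from three parts:
- skin nodules (number, tenderness, inflammation);
- fever, worded as "resolution of ENL-associated fever based on clinical assessment and temperature recordings";
- nerve pain and tenderness, judged by neurological examination and pain instruments.

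No part is conditioned on use of antipyretics or analgesics, and Data Analysis gives no rule for it.

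On sparing, the Introduction (Dovramilast in Relevance to ENL) lists as a secondary question "whether repeated treatment cycles can reduce recurrence without the need for prolonged corticosteroid or thalidomide use". The Discussion (Principal Findings) hypothesises benefit "while reducing reliance on prolonged corticosteroid or thalidomide therapy". The restated question in Methods, Research Question and Hypothesis keeps recurrence but drops the corticosteroid/thalidomide clause. The secondary outcomes cover remission, severity, pain and neurological scales, recurrence, and repeat dovramilast cycles.

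**The concern.** There is no control arm to absorb the effect of co-medication. A participant whose temperature or pain score falls on an antipyretic or analgesic counts towards the dovramilast response in the same way as one who improves without it. The day-10 judgement of response also decides who continues to 28 days or 12 weeks, so it shapes who contributes longer-term data. The article says that the results will guide endpoint choice and sample size for a later randomised trial, so an inflated response proportion would carry forward.

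The sparing question is a different fault. The article asks something that none of its outcomes can answer. A reader of the final report could take low corticosteroid use during dosing as support for the hypothesis, although the protocol itself withholds those regimens then.

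**Working it through.** The article has no power calculation and plans no hypothesis test, so there is no figure to reproduce. The check is a comparison of sections, followed by an illustration on assumed inputs.

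**1. Which response parts the named drugs can move**

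| Part of day-10 response | Open to antipyretics or analgesics? | Condition on their use stated? |
|---|---|---|
| Nodule number and inflammation | Less so | No |
| Nodule tenderness | Possibly | No |
| Fever resolution | Yes | No |
| Nerve pain and tenderness | Yes | No |

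Two of the three parts are directly exposed. In the third part, tenderness may be.

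**2. The sparing question against the outcomes**

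| Section | Corticosteroid/thalidomide use mentioned? |
|---|---|
| Introduction, secondary research question | Yes |
| Discussion, Principal Findings, hypothesis | Yes |
| Methods, Research Question and Hypothesis | No |
| Methods, Aims and Objectives | No |
| Methods, Primary and Secondary Outcomes | No |
| Methods, Data Analysis | No |

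During dosing, absence of these regimens follows from the protocol rule. After dosing, step 1 episodes go to standard care by rule and step 2 episodes go to another dovramilast cycle by rule. All dosed participants are analysed regardless of withdrawal, and no rule covers data collected after another ENL treatment.

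**3. Illustration of the counting rule**

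From the document: up to 40 participants in step 2, and 50 in all with step 1. Assumed, because the document gives neither: an apparent response of 70%, and a share *s* of responders whose fever or pain part is set to not met because of co-medication.

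Reclassified responders: y = x(1 − s), rounded. Proportion: y/n. Exact (Clopper-Pearson) 95% limits: lower = Beta⁻¹(0.025; y, n − y + 1), upper = Beta⁻¹(0.975; y + 1, n − y).

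| s | n = 40 | 95% CI | n = 50 | 95% CI |
|---|---|---|---|---|
| 0 | 28/40 = 70.0% | 53.5 to 83.4 | 35/50 = 70.0% | 55.4 to 82.1 |
| 10% | 25/40 = 62.5% | 45.8 to 77.3 | 32/50 = 64.0% | 49.2 to 77.1 |
| 25% | 21/40 = 52.5% | 36.1 to 68.5 | 26/50 = 52.0% | 37.4 to 66.3 |
| 50% | 14/40 = 35.0% | 20.6 to 51.7 | 18/50 = 36.0% | 22.9 to 50.8 |

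At n = 40 the lower limit lies 70.0 − 53.5 = 16.5 points below the estimate. Reclassifying a quarter of responders moves the estimate by 70.0 − 52.5 = 17.5 points. From about that share upwards, the choice of counting rule matters as much as sampling error. These rows show the effect of a conservative classification. They do not estimate bias, since some reclassified participants would have responded without co-medication.

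**The case against.** Four points can be made on the other side.

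- **Nodules.** The three parts are listed together and joined by *and*. On that reading, fever and pain relief alone cannot make a responder, because nodules must also improve. This stands. A reader might infer that the day-10 result cannot be interpreted at all, and the document does not support that. Exposure is confined to participants who meet the skin part and meet the fever or pain part only because of co-medication.
- **Restrictions.** A reader of the permissive sentence alone might infer that every ENL drug is open during dosing. That is wrong for standard prednisolone and thalidomide regimens, and the 7-day exclusion and the daily-rifampicin rule limit prior treatment as well. The Introduction says that "Prednisolone, thalidomide, and clofazimine are currently recommended by the WHO as treatment for ENL" and lists further agents tried for ENL. No restriction on clofazimine or those further agents is stated, but they are reached only through the open wording, and nothing indicates that participants receive them for ENL.
- **Place in the plan.** Handling of co-medication is often left to the analysis plan, the study is descriptive, and the article concedes the limits of a single-arm design. This has weight, and the absence of a concomitant-medication form or tabulation is not a finding. The mismatch remains, however, because the article itself defines the response and the co-medication rule.
- **Sparing.** The operative Methods sections do not carry the sparing question, and Future Directions speaks of a steroid-sparing option only conditionally. This also stands: that passage is not a claim of effect. The fault lies in the Introduction and Discussion wording, which has no outcome behind it. Nor does the article say what treatment participants removed by day 10 receive, so no argument should rest on that.

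**Conclusion.** The point holds in two limited parts.

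First, as defined, the fever and nerve-pain parts of the day-10 response cannot be attributed to dovramilast separately from permitted antipyretics and analgesics. Nodule number and inflammation are less exposed, so the composite is weakened but keeps some value. The size is unknown. On an assumed 70% apparent response in 40 participants, the proportion falls to between 62.5% and 35% when 10% to 50% of responders are reclassified. Both inputs are assumptions.

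Second, the corticosteroid/thalidomide-sparing question and hypothesis have no matching outcome or analysis, and absence of these drugs during dosing cannot count as evidence. This part rests on the text alone and needs no assumption. Even with an outcome added, a single arm can describe use of these drugs but cannot show that dovramilast reduced it.

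Both parts can be cured by prespecification.

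**What to change.** Leave care unchanged and amend the outcomes and analysis.

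1. Add a secondary outcome: the proportion of all dosed participants given any systemic corticosteroid or thalidomide for ENL from first dose to 12 months after last dose, with total days of use. Report on-drug and off-drug periods separately, and show the two steps apart because their rules for new episodes differ. Describe the result without a sparing claim. Otherwise, delete the sparing wording from the Introduction and from Principal Findings.
2. Report day-10 response on nodule number and inflammation alone, beside the composite.
3. As a sensitivity analysis only, repeat the composite with the fever and pain parts counted as not met when an antipyretic or analgesic was started or increased after baseline, or taken within a prespecified window before scoring.
4. In the remission outcome, count use of another drug given for ENL as loss of remission.

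**Cost.** A few definitions and extra tables, with no added visit or procedure if concomitant-medication dates are recorded. The article does not show whether they are, and step 1 finished in 2020, so its records may not support item 3. The sensitivity response rate will be lower than the main one and may misclassify drugs taken for unrelated reasons, which is why it should not replace the main analysis. The article reports 15 participants recruited by April 2026 and data collection running to September 2027, so the rules can still be fixed before analysis.

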#### Step 1: Evaluation of the Immediate Effects

To evaluate the immediate effects of dovramilast, 10 male participants with moderate to severe, new, or recurrent ENL will receive an initial 10 days of treatment with 200 mg of dovramilast twice daily. The physician has the discretion to determine whether individual prospective participants with severe neuropathy or other severe symptoms should be enrolled. Participants will be males aged 18 to 65 years and weigh greater than or equal to 40 kg. The initial 28-day safety evaluation (step 1) was limited to male participants as a precautionary measure to minimize potential reproductive and pregnancy-related risks during early exposure to dovramilast in patients with ENL. Although dovramilast has demonstrated an acceptable safety profile in previous phase 1 and phase 2 studies in other disease settings, comprehensive reproductive safety data in ENL populations are limited. Restricting early enrollment to males allowed close monitoring of short-term safety and tolerability before broader inclusion. Upon confirmation of acceptable safety by the Data Safety Monitoring Board (DSMB), enrollment was expanded in step 2 to include both male and female participants, with appropriate exclusion of pregnant or breastfeeding women. Safety and efficacy monitoring assessments will be performed by DSMB representative clinicians during the initial 7- to 10-day treatment period. If assessments during the 10-day initial treatment trial indicate poor safety or efficacy, participants may be removed from the treatment no later than day 10. If assessments during the 10-day initial treatment period indicate that the drug is well tolerated and the participant’s ENL symptoms are responding, the treatment will be continued until day 28. If the drug treatment is not well tolerated, or if assessments for efficacy fail to demonstrate ENL symptom relief, participants may be removed from the treatment.

Upon review of the 10- and 28-day assessments, the DSMB will recommend that another cohort of 40 participants be enrolled for up to 12 months of treatment (step 2).

